### Interventions

The trial program outputs two-step reminders of serum lithium monitoring to the treating physician as specified by the algorithm. When a participant in the intervention group visits the outpatient clinic between 4 and 8 months after the last lithium monitoring or at the study registration, reminder A will be sent to the treating physician. If the participant visits within 8 months after reminder A, reminder B will be sent. After reminder B has been sent and the participant visits the clinic thereafter, reminder A will be sent another time. No reminder will be sent if the participant receives lithium monitoring within 4 months, visits the outpatient clinic after 8 months or more, or if the participant is in the control group.

We anticipate that the two-step reminders will improve both the physician’s awareness and the participant’s adherence:
Reminder A

The text of reminder A is as follows: “Please notify the participant of the need for a blood test for serum lithium level at the next outpatient visit. If the next visit will be 8 months or further from the previous blood test, please notify the participant of the need to conduct a blood test today. The participant and the treating physician can decide whether to conduct the blood test.”
Reminder B

The text of reminder B is as follows: “Please notify the participant the need for a blood test for serum lithium level today. The participant and the treating physician can decide whether to conduct the blood test.”

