#### Secondary outcomes

The secondary outcomes are as follows:
The number of blood tests for serum lithium concentration in the 18 months period after the date of informed consent.Exacerbation of major depression or bipolar disorder in the 18-month period from the date of informed consent, defined by at least one of the following: hospitalization; increase in lithium dose; addition of antipsychotic drugs or mood stabilizer (valproic acid, carbamazepine, lamotrigine); or addition of or increase in use of antidepressants.Proportion of days covered (PDC) of lithium carbonate prescription during the 18 months after informed consent [28].Thyroid-stimulating hormone (TSH) ≥ 1.0 μIU/mL after 18 months.Estimated glomerular filtration rate (eGFR) < 60 mL/min per 1.73 m^2^ after 18 months.

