### Assignment of intervention

#### Randomization

The participants will be stratified into nine strata in accordance with the following two conditions in EHR, and automatically randomized by the trial program at their first scheduled visit between 4 and 8 months after informed consent, using permuted block randomization [30].
Diagnosis based on PRIME-MD (major depression, bipolar I disorder, or bipolar II disorder)Serum lithium (between 0.4 mEq/L and 1.0 mEq/L; < 0.4 mEq/L; or > 1.0 mEq/L)

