Second, in our sample size calculation with an EHR-based administrative database including Toyooka hospital, about 45% of patients had serum lithium of < 0.4 mEq/L or > 1.0 mEq/L. We assumed that the infrequent monitoring may partially have caused such deviation. Then, we expect that more frequent monitoring triggered by the reminders may be useful to maintain serum lithium within the appropriate range and achieve subsequent clinical outcomes. The two-step reminders (A and B) are to remind not only the physicians but also the patient. The reminders may, through the increased frequency of the reminder to the physician, the increased awareness on the part of the physicians, the increased recommendation from the physician to the patients based on such reminders, and/or through increased adherence on the part of the patients resulting from such interactions with the physician, help achieve the primary outcome of the therapeutic serum concentration. Then, it is not feasible to mask the patient, because we remind not only the physician to increase the frequency but also the patient to improve adherence. If the automated reminder system is found to be effective for achieving the appropriate serum lithium level in patients taking lithium carbonate in this study, this may contribute directly to improvement in the quality of clinical practice, because its implementation does not require additional effort by clinicians. On the one hand, the trial was so designed to pragmatically examine the net effect of this procedure and not to explore the mechanisms by administering additional questionnaires to the physicians and the patients. This may be a weakness but also a strength in increasing the practicality of the trial and also the generalizability of the final findings through facilitated recruitment.

Finally, both the EHR-nested RCT scheme and the EHR-nested automated reminder system may be applicable in medical specialties other than psychiatry. Overall, if the EHR-nested trial is successful, it can be expected to contribute to the so-called learning healthcare system, where every clinical encounter in routine care can provide an opportunity to expand the evidence base for future health care [31] (Additional file 1).

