### Limitations

We acknowledge some difficulties in the trial. First, “alert fatigue” is possible; when treating physicians are exposed to too many clinical decision support alerts, they may stop responding to the alerts [32]. However, this risk will be relatively low in the present trial, because, in principle, the frequency of reminders is once every 6 months.

Second, because the study will be conducted in a single tertiary care center and randomization will be conducted based on individual patients rather than cluster randomization, the number of blood tests and level of patient adherence may increase in the control group as well as in the intervention group through contamination among the participating physicians. Because the trial is conducted at a single facility, it is difficult to avoid such contamination; however, this is expected to result in underestimation rather than overestimation of the effectiveness of the EHR-reminder system. In future studies, the inclusion of multicenter and cluster randomization may be necessary to minimize this risk.

Third, a clinical endpoint such as exacerbation of mood disorders is more appropriate as the primary outcome than surrogate markers such as serum lithium in a pragmatic trial. However, the expected number of exacerbations is not large within the study period and therefore we do not have enough statistical power to detect the difference in a true endpoint in the trial. On the other hand, another objective of the trial is proof of concept of an EHR-nested RCT in the Japanese setting. A surrogate outcome may be sufficient for the purpose. Then, we chose serum lithium instead of the number of blood tests, one of the secondary outcomes, because it was considered the most clinically relevant among surrogate outcomes.

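### The exacerbation outcome counts every lithium dose increase whatever its reason, so level-driven increases prompted by extra testing can count against the reminder arm

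*Protocol article*

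**What the plan says.** Under Secondary outcomes, the protocol article names as one outcome "Exacerbation of major depression or bipolar disorder in the 18-month period from the date of informed consent". A single event from a list is enough to meet it. That list contains "hospitalization; increase in lithium dose; addition of antipsychotic drugs or mood stabilizer", and also starting or increasing antidepressants. The lithium item carries no condition on symptoms, relapse or reason.

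Under Interventions, reminders go to the treating physician for intervention participants only. Reminder B reads "Please notify the participant the need for a blood test for serum lithium level today" and leaves the decision to test with patient and physician. The Discussion gives the rationale: "we expect that more frequent monitoring triggered by the reminders may be useful to maintain serum lithium within the appropriate range". Being within 0.4 to 1.0 mEq/L at 18 months is the primary outcome.

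Patients below 0.4 mEq/L are enrolled and form a randomization stratum. The treating physician is not masked (Masking). Under Limitations the authors write that "a clinical endpoint such as exacerbation of mood disorders is more appropriate as the primary outcome than surrogate markers", and explain that they chose the surrogate because too few exacerbations are expected for adequate power.

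**The concern.** A dose increase can follow from either of two findings: the patient's mood has worsened, or a blood test has come back low in a patient who is well. Only the first is an exacerbation, but the definition scores both.

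The second kind depends on how often levels are measured, and the intervention acts directly on that. One patient could have a low level found after a reminder, have the dose raised and finish in range. That patient would be a success on the primary outcome and an event on exacerbation. Nothing in the protocol separates the two kinds of increase.

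Exacerbation is the only clinical effectiveness outcome in the list. The other secondary outcomes are a test count, prescription coverage, a TSH threshold and an eGFR threshold. If the component behaves as described, a real reduction in relapse could be hidden, or a neutral effect could look like harm.

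**Working it through.** **1. Does the definition allow the misclassification?** Yes. One listed event is enough, and a lithium increase is listed without qualification.

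**2. Can it differ by arm?** Yes, through testing. Reminders are sent in one arm only, and the Discussion relies on the extra monitoring to bring levels into range. Only levels below 0.4 mEq/L matter here, because correcting a level above 1.0 mEq/L does not call for an increase and so adds no event of this kind.

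**3. What do the documents give for size?** The plan states no figure for exacerbation. The one related figure reproduces: 818/1464 = 55.9% in range, so 646/1464 = 44.1% out of range, which the Discussion rounds to about 45%. Low and high are not separated. No exacerbation rate or dose-change rate is given. Everything in steps 4 and 5 is therefore assumption, shown only for scale.

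**4. Illustration without dilution.** Let e be the true exacerbation rate in the intervention arm. Let d be the extra share of that arm with a level-driven increase, independent of true exacerbation. The observed rate is e + (1 − e)·d. Control is set at 20%, with 60 per group (the planned 120 divided by 2).

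| d | Observed if true rate is 20% | Difference from control | Chance of a nominally significant excess (two-sided 5% test) | Observed if true rate is 10% | Difference from control |
|---|---|---|---|---|---|
| 5% | 24.0% | +4.0 | about 8% | 14.5% | −5.5 |
| 10% | 28.0% | +8.0 | about 17% | 19.0% | −1.0 |
| 12.5% | 30.0% | +10.0 | about 24% | 21.25% | +1.25 |
| 20% | 36.0% | +16.0 | about 50% | 28.0% | +8.0 |
| 25% | 40.0% | +20.0 | about 67% | 32.5% | +12.5 |

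For reference, d = 25% would mean that dose increases equal the whole planned gain in the primary outcome (80% − 55% = 25 points), leaving nothing to adherence. That is an extreme case. A true halving from 20% to 10% disappears when 0.10 + 0.90·d = 0.20, that is, at d = 11.1%. With a true rate of 10% or 30% in both arms, the shift at d = 10% is 0.90 × 10 = 9 points or 0.70 × 10 = 7 points.

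**5. Illustration with the common baseline test.** Assume 30% of participants are below 0.4 mEq/L, 20% truly exacerbate, and reminders lead to an increase in a fraction g of those low.

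- No baseline correction: 1 − 0.80 × (1 − 0.30·g) gives 24.8% at g = 0.2 and 32.0% at g = 0.5, against 20% in control. The excess is 4.8 to 12.0 points.
- Half of the low patients (15% of all) already increased in both arms after the baseline test: control is 1 − 0.80 × 0.85 = 32.0%. Intervention is 1 − 0.80 × (0.85 − 0.15·g), which is 34.4% at g = 0.2 and 38.0% at g = 0.5. The excess is 2.4 to 6.0 points.

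Under this assumption the common baseline test halves the excess.

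**6. Window.** Events count from consent, but participants are "automatically randomized by the trial program at their first scheduled visit between 4 and 8 months after informed consent". Only 18 − 8 = 10 to 18 − 4 = 14 of the 18 months can differ by arm. Earlier events add equally to both.

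**The case against.** A reader might infer that the reminder is meant to trigger dose increases and that the outcome is therefore biased by construction. The documents do not support that. The reminder texts ask only for a blood test. The Discussion names physician awareness, recommendation to the patient and patient adherence as routes, and a level that rises through better adherence produces no event. No passage says that a low level is to be answered by a dose increase. This objection stands. The mechanism is possible and has a direction, but it is not written into the design.

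The baseline test is a second strong point. Candidates are screened because they lack a recent level, and all must then have one within 7 days of consent (Eligibility check and registration). Physicians in both arms therefore know of low levels months before allocation. Increases made in response fall inside the window in both arms and leave fewer low patients for a reminder to expose. Contamination of controls, acknowledged under Limitations, narrows the gap further. These points reduce the size but do not remove the difference in later testing, which is the purpose of the intervention.

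Third, a dose increase is also a genuine response to relapse, so it would be wrong to say that the component is no marker of exacerbation. It is a mixed marker, and removing it loses some true events from an outcome with few. This stands as a cost of the fix.

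Finally, the outcome is secondary, secondary analyses are declared exploratory (Statistical analysis), and the authors say that power for it is insufficient. This limits the consequence. It does not justify a definition that can push the comparison in one direction.

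**Conclusion.** The concern holds in a limited form. The definition counts every lithium dose increase, and extra testing in one arm can make level-driven increases more frequent there. The likely direction is against the intervention, in the trial's only clinical effectiveness outcome.

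The size cannot be derived from the protocol. The shift is about (1 − e)·d, and neither quantity is given. The illustrations run from about 2 points, with dilution by the baseline test, to 20 points in the extreme case. None of these is an estimate for this trial. They assume a 20% true rate, independence of level-driven increases from true exacerbation, and chosen shares of low and adjusted patients.

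A reader might also infer that the trial's main result is compromised. It is not: the primary outcome, its analysis and the sample size do not use this definition. The change is worth making because it is cheap, but the primary conclusion does not depend on it.

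**What to change.** Before unmasking, in the outcome definition and the analysis plan:

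- Analyse exacerbation without the lithium dose component, keeping hospitalization and the other listed drug changes. Counting a lithium increase only when another listed event also occurs gives the same yes/no result, because that other event already makes the patient a case.
- Report lithium dose increases by arm as a separate process outcome.
- Keep the present composite as a sensitivity analysis, so that readers can see how much the component contributes.

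The cost is a change of definition, with the approvals set out under Protocol amendments. The data are already in the EHR, and no visit, test or sample-size change is needed. The downside is that relapses treated only by raising lithium are not counted in the revised outcome; the sensitivity analysis still shows them. The change concerns scoring only and implies no rule about lithium dosing.

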**Fig. 1 Fig1:**
[figure not shown]
Flow diagram of the trial. Exclusion criteria 12 and 13 are confirmed after informed consent, but before randomization. ICD: *International classification of disease*, DSM: *Diagnostic and Statistical Manual of Mental Disorders*

**Table 1 Tab1:** Schedule of the enrollment, intervention, and assessments

	Study periods							
		Enrollment	Allocation	Post-allocation				Close-out
	Timepoints	T_-1_	T_0_	T_1-A_	T_1-B_	T_2-A_	T_2-B_	T_x_^e^
Trial program	Enrollment							
	Screening	X						
	Randomization^a^		X					
	Intervention							
	Reminder A			X		X		
	Reminder B				X		X	
	Assessments							
	Baseline characteristics^b^	X						
Treating physician	Enrollment							
	PRIME-MD^c^	X						
	Eligibility assessment	X						
	Informed consent	X						
	Assessments							
	Lithium concentration^d^	X						X
	Liver function	X						X
	Kidney function	X						X
	Thyroid function							X

*PRIME-MD* Primary Care Evaluation of Mental Disorders

^a^Stratified block randomization will be conducted if the candidate has a measurement of serum lithium within 7 days of giving informed consent and an appointment between 4 and 8 months after giving informed consent

^b^Basic information includes gender, age, and concomitant medication

^c^The candidate will be classified as having major depression, bipolar I disorder, or bipolar II disorder

^d^Serum lithium will be classified into three groups (between 0.4 mEq/L and 1.0 mEq/L inclusive; < 0.4 mEq/L; or > 1.0 mEq/L)

^e^The first scheduled visit is between 18 and 24 months after informed consent

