#### Eligibility check and registration

Primary Care Evaluation of Mental Disorders (PRIME-MD) is a semi-structured diagnostic tool to assist primary care physicians in the diagnosis of common mental disorders based on the DSM-5 [29]. The treating physician conducts the PRIME-MD and confirms the diagnosis of depression, bipolar I, or bipolar II. If the candidate meets the eligibility criteria and written informed consent is obtained, the treating physician registers the participant through the EHR. If the candidate is not eligible, refuses participation, or withdraws after participation, the treating physician enters the status through EHR. The treating physician will conduct a baseline blood test within 7 days of the patient giving informed consent. If the candidate does not receive the baseline blood test or a measurement of serum lithium is not available within 7 days, he/she will be excluded from the study.

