### Foreseeable adverse events

No adverse events are foreseeable for the trial intervention itself, except for the potential burden and complications of blood tests. All drugs, including lithium carbonate, are within the approved dosages and indications according to the MHLW.

The foreseeable side effects of lithium carbonate, as described in the package insert, are as follows:

Major side effects: Tremor (4.6%), dry mouth (2.4%), and diarrhea (1.2%). Serious side effects: Lithium intoxication (unknown frequency); malignant syndrome (unknown frequency); sick sinus syndrome and bradycardia (unknown frequency); nephrotic diabetes insipidus (unknown frequency); acute kidney injury, interstitial nephritis, and nephrotic syndrome (unknown frequency); hypothyroidism and thyroiditis (unknown frequency); hyperparathyroidism (frequency unknown); and dementia and impaired consciousness (frequency unknown).

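### TSH at 18 months is a secondary outcome, but Table 1 schedules no thyroid test before allocation, so the scheduled data cannot adjust for prior abnormality or separate it from new abnormality (minor)

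*Protocol article*

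**What the plan says.** Under Secondary outcomes the protocol article lists two laboratory outcomes of the same form: "Thyroid-stimulating hormone (TSH) ≥ 1.0 μIU/mL after 18 months" and "Estimated glomerular filtration rate (eGFR) < 60 mL/min per 1.73 m^2^ after 18 months". Both are a yes/no status at the end of follow-up. Neither is a change from baseline or a new-onset event.

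In Table 1 the row "Kidney function" is marked at enrollment and at close-out, as are serum lithium and "Liver function". The row "Thyroid function" is marked at close-out only.

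No other part of the article supplies a baseline thyroid value. The footnote on baseline characteristics reads "Basic information includes gender, age, and concomitant medication". The section on eligibility check and registration says "The treating physician will conduct a baseline blood test within 7 days of the patient giving informed consent" and does not mention TSH there. The exclusion criteria name no thyroid disease, and the randomization strata are diagnosis and serum lithium class. The section on foreseeable adverse events lists "hypothyroidism and thyroiditis (unknown frequency") among the serious side effects of lithium.

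**The concern.** Everyone enters after at least 6 months on a drug that the protocol itself links to hypothyroidism, and randomization follows consent by a further 4 to 8 months. Some participants may therefore already meet the TSH criterion when they are allocated. If they still meet it at close-out they count as events in either arm, and the scheduled data hold nothing that identifies them.

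Two things are at stake. First, precision: a known source of between-person variation in the outcome is left in the comparison, and a chance imbalance in it can be neither displayed nor adjusted for. Second, interpretation: an abnormal TSH at close-out cannot be classed as carried in or as arising during the trial. The eGFR outcome does not have this gap, because kidney function is measured at enrollment.

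An analysis plan can choose how to use a baseline value, but it cannot create one that was not measured. That is why the schedule itself matters.

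**Working it through.** The article states no figure on this point, so there is none to reproduce. The check sets the outcome list against the schedule and then sizes the consequence under stated assumptions.

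**Step 1. Schedule against outcomes (Table 1 and the outcome lists)**

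| Test | Enrollment | Close-out | Used by a listed outcome |
|---|---|---|---|
| Serum lithium | yes | yes | primary |
| Kidney function | yes | yes | secondary (eGFR) |
| Thyroid function | no | yes | secondary (TSH) |
| Liver function | yes | yes | none |

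**Step 2. Timing.** Lithium exposure is at least 6 months at consent, and allocation is 4–8 months later, so exposure before allocation is at least 6 + 4 = 10 months. Close-out is 18–24 months after consent, hence between 18 − 8 = 10 and 24 − 4 = 20 months after allocation.

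**Step 3. Chance imbalance at entry.** Inputs: 60 per arm (half of the planned 120); proportion p already meeting the criterion, not given in the article and therefore assumed.

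SD of the difference = √(2p(1−p)/60)

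- p = 10%: √(2 × 0.1 × 0.9/60) = 5.5 points; 1.96 SD = 10.7 points; 6 participants per arm
- p = 20%: √(2 × 0.2 × 0.8/60) = 7.3 points; 1.96 SD = 14.3 points; 12 participants per arm
- wider range, since the article gives no prevalence at its cut-off: p = 30% gives 8.4 points and p = 50% gives 9.1 points

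This imbalance is part of the ordinary sampling error of the close-out comparison, not an addition to it. An unadjusted confidence interval already covers it.

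**Step 4. What adjustment would recover.** Assumptions: bivariate normal baseline and final TSH (after a suitable transformation) with correlation r = 0.6–0.7, and the same p at both times. Let c be the normal cut-off with upper tail p, and φ(c) the normal density there.

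- Linear adjustment of the binary outcome for continuous baseline TSH removes a share r²φ(c)²/(p(1−p)) of its variance. For p = 10%, φ(c) = 0.1755: 12% (r = 0.6) to 17% (r = 0.7). For p = 20%, φ(c) = 0.2800: 18% to 24%.
- Adjustment for baseline status (yes/no) removes [(p₁₁ − p²)/(p(1−p))]², where p₁₁ is the probability of meeting the criterion at both times. For p = 10%, p₁₁ = 0.039 to 0.047: 10% to 17%. For p = 20%, p₁₁ = 0.099 to 0.113: 14% to 21%.

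The overall range is 10–24% of the variance. The standard error of a risk difference would fall by 1 − √0.90 = 5% to 1 − √0.76 = 13%.

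**Step 5. Interpretation.** Suppose 30% meet the criterion at close-out (illustration only), and that those who met it at entry (share b) still do. The new-onset risk among the others is (0.30 − b)/(1 − b): 30% for b = 0, 22% for b = 10%, 12.5% for b = 20%. Close-out data alone cannot tell these apart.

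**The case against.** The strongest reply is that nothing contradicts anything. The outcome is defined as a status at 18 months, Table 1 schedules the one value that definition needs, and randomization balances prior abnormality in expectation. The comparison is therefore valid as planned, and asking for a baseline is a wish for more precision on one of five secondary outcomes that the article calls exploratory. This stands, and it sets the weight of the point. It does not remove the gap, because the parallel eGFR outcome has the baseline and the blood is already being drawn.

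A reader might also infer more than the article supports:

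- **That the comparison is biased, or that the outcome mostly reflects status before randomization.** The article gives no prevalence. Even the assumed 10–20% leaves 80–90% below the criterion at entry.
- **That no adjustment is possible.** The data management section has researchers extract data from the EHR as well as from the trial program, so routine TSH values may exist for some participants. Recorded concomitant medication might also show thyroid treatment. What is missing is a scheduled value and a stated plan to use the others.
- **That taking liver tests twice is a mistake because no outcome uses them.** The limitations section names the final blood test as a source for non-serious adverse events, so they have a plausible safety use.
- **That adjustment would save r² = 36–49% of the variance.** That formula is for a continuous endpoint. For the binary outcome the saving is the 10–24% shown above. In a logistic model, adjustment does not shrink the variance of the log odds ratio in that way at all.

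Finally, 101 of the planned 120 were already recruited by 11 September 2019, so a new enrollment test covers about 19 people (16%). That limits the remedy. However, because allocation follows consent by at least 4 months, anyone who consented after about 11 May 2019 could not yet have been randomized on that date and could still be tested beforehand.

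**Conclusion.** The point holds as a minor one. Followed as written, the schedule leaves a declared secondary outcome without a pre-allocation value, in patients already exposed to a drug with a listed thyroid effect. The between-arm comparison of close-out status remains unbiased in expectation. The cost is a modest loss of precision, no means in the scheduled data of showing or adjusting for a chance imbalance, and no separation of prior from new abnormality. The sizes in the working depend on an assumed entry prevalence of 10–20%, an assumed correlation of 0.6–0.7 and bivariate normality; none of these comes from the article. The primary outcome and its analysis are untouched.

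**What to change.** - Mark thyroid function in the enrollment column of Table 1 for participants still to be enrolled, run on the baseline blood sample already taken.
- For participants who have consented but are not yet randomized, obtain TSH before allocation.
- For those already randomized, prespecify extraction of the last pre-randomization TSH from the EHR where one exists.
- Adjust the exploratory thyroid analysis for this value rather than restricting it to participants normal at entry, so that all participants stay in the comparison. Where no baseline exists, describe the result as prevalence at close-out and do not present it as new-onset abnormality.

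Cost: one extra analyte on an existing draw and one EHR query. Downside: the baseline will be incomplete for many of the 101 participants already recruited, since it then depends on what routine care happened to measure. An enrollment value also precedes allocation by 4 to 8 months; it is a legitimate covariate but does not give status on the day of randomization.

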### Sample size calculation

We estimated the sample size using Real World Data (RWD) database (Health, Clinic, Education, Information Evaluation Institute/Real World Data, Co., Ltd). Toyooka Hospital provides anonymized patient data to the database, which includes about 19 million patients’ data from 170 institutions in Japan. In RWD database, 1464 patients were prescribed lithium carbonate in a 6-month period. Of those, serum lithium was maintained between 0.4 mEq/L and 1.0 mEq/L in 818 (55.9%) patients. Although RWD database includes patients from Toyooka Hospital, the number of patients in Toyooka Hospital is unclear because numbers of patients in each hospital were not provided to the researcher.

In the trial, we assumed that 80% of participants in the intervention group and 55% of patients in the control group will achieve the goal. As 54 participants are needed for each group, assuming a dropout rate of 10%, a total of 120 participants is required to detect this difference with a type I error of 5% and a type II error of 10%, using the two-sided chi-square test.

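### The secondary thyroid outcome, TSH ≥ 1.0 μIU/mL, cannot distinguish hypothyroid from unaffected participants

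*Protocol article*

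**What the plan says.** The fourth item under Secondary outcomes is "Thyroid-stimulating hormone (TSH) ≥ 1.0" μIU/mL after 18 months. The next item is the renal counterpart, "Estimated glomerular filtration rate (eGFR) < 60 mL/min" per 1.73 m², also after 18 months. Neither has an explanatory note, and no other section of the article gives a TSH reference range, a reason for the value 1.0 or a different cut-off.

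Foreseeable adverse events lists, among the serious side effects of lithium taken from the package insert, "hypothyroidism and thyroiditis (unknown frequency").

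In Table 1 the row "Thyroid function" is marked at close-out only, whereas lithium concentration, liver function and kidney function are marked at enrollment as well. Statistical analysis describes secondary analyses as exploratory, without adjustment for multiple testing.

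**The concern.** The article does not say in words what the TSH outcome is for, but three features point the same way. The rule counts high values. It stands next to a one-sided abnormality threshold for the kidney. The article itself lists hypothyroidism as a harm of lithium. Raised TSH as a sign of thyroid harm is the reading that fits all three.

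A marker of that kind needs a cut-off that unaffected people seldom reach. A value of 1.0 μIU/mL lies inside every adult reference interval assumed below, and close to or under the median that each implies. Followed as written, the rule would count many unaffected participants as events in both arms. The arms could then look alike although thyroid harm differed, and the raw rate could be read as a very high prevalence of abnormal thyroid function.

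**Working it through.** The cut-off is a definition, so the plan has no derived figure to reproduce. The check asks how many unaffected people would meet the rule, and what that does to a comparison of the arms.

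**Inputs from the article.** Cut-off 1.0 μIU/mL (Secondary outcomes). Arm size 54 before dropout (Sample size calculation: "As 54 participants are needed for each group"), borrowed here only as a realistic number per arm. Two-sided 5% test. (Whether 54 matches the stated type II error is a separate matter and does not bear on this point.)

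**Assumptions not in the article.** TSH is log-normal in unaffected people, with a reference interval (L, U) marking the 2.5th and 97.5th percentiles. Several intervals are tried. All hypothyroid participants are taken to have TSH ≥ 1.0.

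**Step 1: share of unaffected people at or above 1.0.** On the log scale, mean m = (ln L + ln U)/2 and s = (ln U − ln L)/3.92. Since ln 1.0 = 0, q = P(TSH ≥ 1.0) = Φ(m/s). For 0.4–4.0: m = (−0.916 + 1.386)/2 = 0.235, s = 2.303/3.92 = 0.587, m/s = 0.400, q = 65.5%.

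| Assumed interval (μIU/mL) | Implied median | q |
|---|---|---|
| 0.3–3.0 | 0.95 | 46.4% |
| 0.4–4.0 | 1.26 | 65.5% |
| 0.45–4.5 | 1.42 | 72.6% |
| 0.5–5.0 | 1.58 | 78.2% |
| 0.6–4.5 | 1.64 | 83.3% |

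By construction 2.5% of the same people exceed U. In a healthy population the rule would therefore flag between 46.4/2.5 ≈ 19 and 83.3/2.5 ≈ 33 people for each one above the upper limit.

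**Step 2: effect on the contrast between arms.** If a share h of an arm is hypothyroid, the observed event rate is h + (1 − h)q. The difference between arms is then

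[h₂ + (1 − h₂)q] − [h₁ + (1 − h₁)q] = (h₂ − h₁)(1 − q).

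**Step 3: illustration.** Take assumed hypothyroidism rates of 10% and 25%, with 54 per arm. Power is Φ{(|d|√n − 1.96√[2p̄(1 − p̄)])/√[p₁(1 − p₁) + p₂(1 − p₂)]}, where d = p₂ − p₁ and p̄ is the mean of the two rates. The last column is h/(h + (1 − h)q) in the 10% arm.

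| Rule | Event rates | Difference | Power | Share of events truly hypothyroid (10% arm) |
|---|---|---|---|---|
| Hypothyroidism counted directly | 10.0% vs 25.0% | 15.0 points | 54% | 100% |
| q = 50% | 55.0% vs 62.5% | 7.5 | 12% | 18% |
| q = 60% | 64.0% vs 70.0% | 6.0 | 10% | 16% |
| q = 70% | 73.0% vs 77.5% | 4.5 | 8% | 14% |
| q = 80% | 82.0% vs 85.0% | 3.0 | 6% | 12% |

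Other assumed rates give the same pattern. For 10% vs 30%, power is 75% counted directly and falls from 18% to 8% as q goes from 50% to 80%. For 5% vs 15%, it is 41% counted directly and falls from 8% to 5%.

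**The case against.** The strongest objection is that the premise comes from outside the document. The article gives no TSH distribution, and the shares above rest on assumed intervals and a log-normal shape. They also describe healthy adults, while participants have taken lithium for at least 6 months. This stands as a limit on precision: neither q nor the ratio in step 1 predicts the rates this trial will observe. It does not rescue the cut-off, because even the lowest interval tried leaves nearly half of unaffected people counted as events.

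The purpose of the outcome is inferred, and the list under Foreseeable adverse events is not an outcome rationale. That is fair, but nothing in the article supports another reading.

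Four stronger readings are tempting and are not supported:

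- **That the outcome cannot detect hypothyroidism.** A participant with raised TSH still meets the rule. The failure is of specificity and of contrast between arms.
- **That most unaffected participants, or well over half, would be events.** The lowest interval gives 46%. About half to four-fifths is what the assumptions support.
- **That the value is a decimal slip.** A misprint is possible, but the article offers nothing to confirm it.
- **That the lack of a scheduled baseline TSH biases the comparison.** Randomization balances existing cases in expectation, so a close-out comparison remains valid. The cost is precision and the ability to separate new from existing cases.

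Finally, the outcome is one of five secondary outcomes, all exploratory. That limits the weight of the point, not its correctness.

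**Conclusion.** The point holds in this form: the article states a thyroid outcome rule that cannot distinguish hypothyroid from unaffected participants. With log-normal TSH and assumed reference intervals from 0.3–3.0 to 0.6–4.5 μIU/mL, 46–83% of unaffected participants would meet it, so a true difference between arms would keep only 54% (1 − 0.46) to 17% (1 − 0.83) of its size. In the 10% vs 25% illustration, power falls from 54% to between 12% and 6%; those hypothyroidism rates are assumptions, not forecasts.

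This is not a detail left to the analysis plan, since the threshold is stated. The conclusion rests on reading the outcome as a marker of thyroid harm, which the article implies but does not say. The primary outcome, the sample size and the randomization do not depend on it. It should be corrected, but it does not threaten the trial's main result.

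**What to change.** Check the cut-off against the ethics-approved protocol and correct it before outcomes are analysed. Define the outcome as TSH above the upper limit of the hospital laboratory's reference range, state that range, and say in one sentence what the outcome is meant to measure. Add log(TSH) at close-out, compared between arms, as a supporting continuous analysis; it uses the whole distribution and needs no threshold.

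The cost is one corrected definition, carried into any other trial document that repeats it. No new tests are needed, because Table 1 already schedules thyroid function at close-out. The timing allowed for this when the article appeared in December 2019: recruitment began in November 2018 and the final evaluation falls 18 to 24 months after consent, so the first close-out values were not due before May 2020.

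The downside is fewer events. The binary comparison will be descriptive and should be reported as such, with the continuous analysis beside it.
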